### Sample size {14}

In the GREAT trial, the mean score for goal attainment at baseline was approximately 3.5 (SD 1.6) [55]. To detect a standardised effect size of 0.5 between groups (regarded as a moderate effect size [57] with 90% power, we would need 85 in each group. To allow for 20% attrition, this sample size has been inflated to give a total sample size of 214, with 107 patients in each arm. In terms of caregivers, a previous study has estimated that up to 80% of people with moderate to advanced Parkinson’s have an informal caregiver [58]. If 80% of the 214 recruited patient participants have an informal caregiver and 70% of these agree to take part, this would result in 120 caregiver participants (60 in each arm). With this number of caregiver participants, we could detect a difference of half a standard deviation in the primary outcome measure with 80% power and at a 5% significance level. This is equivalent to a 9 point difference in the CES index score, based on Rand et al. who reported a mean CES index score of 68.70 with a standard deviation of 17.78 amongst carers of adults using social care support in England [59]. We will have slightly greater power because we will recruit up to 3 caregivers per patient, although these will not be independent observations

Patients will be recruited predominantly through three routes. The first is where they will have expressed written interest in hearing about further research on a consent form through participating in other research studies. Secondly, they may be identified by the trial team from current hospital admissions or clinic lists. Thirdly, they may hear about the trial through local advertising or on social media. Potential participants will be sent an invitation pack containing a letter of invitation, a Patient Information Brochure, a pre-paid reply slip and a consent form, which is for information only. It will also include the equivalent documents for a potential caregiver who may wish to take part. If the team has not heard from the potential participant within 2 weeks of posting the invitation pack to them, they will receive a phone call and all questions will be answered. Potential participants and caregivers who indicate that they are interested in taking part, either by phone or by posting back the reply slip(s), will receive an appointment letter for Visit 1 with the relevant questionnaire booklet or a link to electronic questionnaires, depending on their preference.

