## Statistical methods

### Statistical methods for primary and secondary outcomes {20a}

To determine if PRIME Parkinson care can improve goal attainment and impact the secondary outcomes, the primary analysis to determine whether PRIME Parkinson care can achieve goal attainment and improve health-related quality of life, symptom burden and hospitalisations will be conducted according to the intention to treat principle. Participants who provide primary outcome data will be included in the analysis in their allocated group (see below concerning missing outcome data). The intervention effect will be estimated as the coefficient of a binary covariate indicating treatment allocation in a linear regression with the goal attainment score as the outcome variable and with age and Hoehn and Yahr stage (minimisation variables) as additional covariates. We will examine the outcome at 24 months first, and if we observe no benefit, we will test if this was observed at 12 months. The estimated effect will be presented together with 95% confidence intervals and *p*-value. This approach to the analysis will be adapted to the participant secondary outcome measures, and to the outcome measures completed by caregivers. To determine the effect of PRIME Parkinson care versus usual care on those caring for, living with, or supporting a person with parkinsonism, robust standard errors will be employed to accommodate correlation between caregivers of the same participant.

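### Goal attainment is tested at 12 months only if 24 months shows no benefit, with no alpha split and no secondary label; if a 12-month result may count as success, the false-benefit rate rises from 2.5% to about 4-5%

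*Protocol article*

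**What the plan says.** Statistical methods {20a} sets the order of testing for goal attainment: the team will "examine the outcome at 24 months first, and if we observe no benefit, we will test if this was observed at 12 months". On reporting it says: "The estimated effect will be presented together with 95% confidence intervals", with a p-value. It mentions no division of the significance level between the two time points, and does not call the 12-month test secondary or exploratory. It then continues: "This approach to the analysis will be adapted to the participant secondary outcome measures, and to the outcome measures completed by caregivers".

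Outcomes {12} names goal attainment as the patient primary outcome, measured every three months, without singling out one time point as primary. The intervention lasts 24 months (Participant timeline {13}), and Plans for assessment {18a} places the 12-month assessment at the mid-point.

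Sample size {14} is built on one comparison: "To detect a standardised effect size of 0.5 between groups" and "with 90% power, we would need 85 in each group". It then adds: "To allow for 20% attrition, this sample size has been inflated to give a total sample size of 214, with 107 patients in each arm". A significance level appears only in the caregiver calculation: "with 80% power and at a 5% significance level".

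**The concern.** In a fixed-sequence procedure the second hypothesis is tested only after the first has been rejected. A false claim then requires the first test to be wrong, so the overall error stays at 5% with no adjustment. Here the second test is reached when the first has not shown benefit. Each time point gets the full 5%, and the second look adds to the error of the first.

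The trigger is the absence of benefit at 24 months. That covers a null result and also one favouring usual care. If the 12-month test can carry the primary claim, an effect seen halfway through the intervention could be presented as success although nothing, or the opposite, was found at the end. What is at stake is the error rate of the trial's main claim and what that claim means.

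**Working it through.** **1. The plan's own figure.** Inputs from Sample size {14}: standardised difference 0.5, power 90%, attrition 20%. With a two-sided 5% test (normal approximation):

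n per arm = 2(1.960 + 1.282)² / 0.5² = 2 × 10.51 / 0.25 = 84.1, rounded up to 85.

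Inflated for attrition: 85 / 0.8 = 106.25, rounded up to 107 per arm, 214 in total. Both stated figures reproduce. A one-sided 5% test would give 2(1.645 + 1.282)² / 0.25 = 68.5, so 69 per arm. Two-sided 2.5% would give 2(2.241 + 1.282)² / 0.25 = 99.3, so 100 per arm. The stated size therefore fits one test at the full two-sided 5%, with nothing reserved for a second.

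**2. Error across the two tests.** Let Z24 and Z12 be the test statistics, standard normal under the null of no effect at either time, with correlation ρ. Take no benefit to mean no significant result in favour of PRIME.

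- False claim of benefit: P(Z24 > 1.96 or Z12 > 1.96) = 1 − Φ₂(1.96, 1.96; ρ). The nominal rate is 2.5%.
- Any rejection in either direction: 1 − P(|Z24| ≤ 1.96 and |Z12| ≤ 1.96). The nominal rate is 5%.

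The article gives no ρ, so a range is shown.

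| ρ (assumed) | False benefit | Any rejection |
|---|---|---|
| 0 (independent) | 4.94% | 9.75% |
| 0.3 | 4.76% | 9.51% |
| 0.5 | 4.54% | 9.07% |
| 0.7 | 4.17% | 8.35% |
| 0.8 | 3.90% | 7.81% |
| 0.9 | 3.52% | 7.04% |

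Over ρ from 0.8 to 0.3 the false-benefit rate is 3.9 / 2.5 = 1.6 to 4.8 / 2.5 = 1.9 times nominal. The inflation shrinks as ρ rises but is still present at 0.9.

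**3. Sensitivity to the trigger.** The article does not define no benefit. Suppose it means a 24-month estimate at or below zero. The false-benefit rate is then 0.025 + P(Z24 ≤ 0 and Z12 > 1.96), which is 3.1%, 2.7% and 2.5% at ρ = 0.3, 0.5 and 0.7. The inflation is then small, but the only route to a 12-month claim is through a 24-month estimate that is null or adverse.

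**4. Alternatives.** With 24 months as the only primary test, or with 12 months tested only after success at 24 months, the two-sided rate under this null is 5%. With 2.5% at each time point it is 4.94% under independence and lower for positive ρ. Power at 85 per arm then falls from 90.3% to 84.6%. Restoring 90% would need 100 per arm, or 100 / 0.8 = 125 per arm and 250 in total after attrition.

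**The case against.** The strongest reply is that the article never says a positive 12-month result makes the trial positive. It puts 24 months first, and the 12-month question can be read as asking whether there was a transient effect after a null primary result. On that reading the primary claim keeps its 5%. This stands as a possible reading, and the inflation is conditional on the other one. But the 12-month test is described as a test of the primary outcome, in the paragraph on the primary analysis, with nothing marking it as secondary. An analysis plan may settle its status; the order of testing, however, is fixed here.

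A second reply is that the rule is directional, so the relevant error is false benefit, which stays below 5%. That is right, and a reader who infers an 8% to 9.5% chance of a false win would be mistaken. Those figures include significant results favouring usual care, and they hold only for ρ of about 0.77 down to 0.31. The proper comparison is still with 2.5%, the benefit-side share of the two-sided 5% on which the trial is sized.

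Three stronger readings are tempting, and the article does not support them:

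- That the successful time point is picked after seeing the data. Both time points and their order are set in advance, so this is an unadjusted fallback and not post hoc selection.
- That the 12-month result goes unreported if 24 months succeeds. Outcomes {12} has the mean rating calculated at every evaluation point; only the formal test is conditional.
- That every secondary outcome goes through the same two-step rule. The text says only that the approach will be adapted, which may refer just to the regression model.

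Finally, the Discussion presents the trial as an early evaluation and looks to a later cluster trial for stronger evidence. That lowers the stakes but does not resolve the ambiguity.

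**Conclusion.** The point holds in conditional form. The stated order reverses a valid fixed sequence, and the status of the 12-month test is left open. If that test may support the primary claim, and no benefit means not significantly better, the false-benefit rate is about 3.9% to 4.8% against 2.5% (any rejection: about 7.8% to 9.5% against 5%) for an assumed ρ of 0.8 down to 0.3. If the 12-month test is only secondary, the primary claim is not inflated, but the article does not say so. The treatment estimates, the regression model and the data collection are unaffected.

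**What to change.** In {20a}, replace the conditional rule with wording such as: goal attainment at 24 months is the sole primary analysis, tested at two-sided 5%; the 12-month effect is estimated and reported in every case as a secondary result and cannot by itself support a claim of benefit. If a confirmatory 12-month claim is wanted, test it at 5% only after 24 months is significant. Use the same wording for the caregiver primary outcome and wherever the approach is adapted to secondary outcomes. Settle this before outcome data are seen.

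The cost is one or two sentences, with no extra patients and no loss of power at 24 months. The downside is that the fallback route to a positive claim is lost. Keeping it with an even alpha split would carry the power or recruitment cost shown in step 4 of the working.

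### Equal-weight regression of caregiver outcomes loses precision when patients have different numbers of caregivers, so the small power gain expected from up to three per patient is not assured

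*Protocol article*

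**What the plan says.** Statistical methods {20a} of the protocol article defines the estimator for the main analysis: "The intervention effect will be estimated as the coefficient of a binary covariate indicating treatment allocation in a linear regression", adjusted for the minimisation variables. The same approach is to be adapted to the outcomes that caregivers complete. For clustering it names one device: "robust standard errors will be employed to accommodate correlation between caregivers of the same participant". It mentions no weights, random effect or working correlation.

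Sample size {14} derives the caregiver number as follows: "If 80% of the 214 recruited patient participants have an informal caregiver and 70% of these agree to take part", there will be 120 caregivers, 60 per arm. That is in effect one caregiver per participating patient. With this number, the article says, "we could detect a difference of half a standard deviation in the primary outcome measure with 80% power and at a 5% significance level". It then adds: "We will have slightly greater power because we will recruit up to 3 caregivers per patient, although these will not be independent observations".

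No ICC and no expected distribution of caregivers per patient is given.

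**The concern.** Robust standard errors change the standard error but not the point estimate. A linear regression with robust errors therefore still gives a family of three caregivers (three caregivers of the same patient) three times the weight of a family of one. If the three answers are strongly correlated, they carry little more information than one answer, and the threefold weight adds variance to the estimated effect. Recruiting extra caregivers can then leave the comparison less precise than recruiting one each.

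The caregiver effect is a stated objective with its own primary outcome, the Carer Experience Scale. The planned number gives slightly under the stated 80% power, so there is little margin. The question is whether the expected gain follows from the stated analysis.

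**Working it through.** **Inputs from Sample size {14}.** 214 × 0.80 × 0.70 = 119.8 caregivers, so 60 per arm; difference 0.5 SD; 5% significance, taken as two-sided; SD 17.78, so 0.5 SD = 8.89 points, given as 9.

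**Reproducing the stated power.** Normal approximation: power = Φ(0.5 × √(60/2) − 1.96) = Φ(0.779) = 78.2%. With 9 points and SD 17.78 it is 79.2%. The noncentral t gives 77.5%. The stated 80% is reproduced to within rounding. The reference below is 78.2%, for 60 families per arm with one caregiver each.

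**Assumptions.** The mix of family sizes and the ICC (ρ) are not in the article and are varied here. The number of families is held at 60 per arm, and covariates and caregiver attrition are left out.

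**Formulas.** Let m be the number of caregivers in a family and μ the mean of m.
- Equal weighting: effective n per arm = 60 × μ² / (μ + ρ·E[m(m−1)]).
- Exchangeable weighting with ρ known: effective n per arm = 60 × E[m / (1 + (m−1)ρ)].
- Equal weighting falls below 60 when ρ exceeds μ(μ−1) / E[m(m−1)].

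**Worked case: 80/15/5% of families with 1/2/3 caregivers.** μ = 0.80 + 0.30 + 0.15 = 1.25. E[m(m−1)] = 0.15×2 + 0.05×6 = 0.60. Break-even ρ = 1.25 × 0.25 / 0.60 = 0.52.

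| ρ | Effective n, equal weights | Power | Effective n, exchangeable | Power |
|---|---|---|---|---|
| 0.3 | 93.75/1.43 = 65.6 | 81.7% | 67.5 | 82.7% |
| 0.5 | 93.75/1.55 = 60.5 | 78.5% | 64.5 | 81.0% |
| 0.7 | 93.75/1.67 = 56.1 | 75.5% | 62.3 | 79.7% |

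Here 93.75 = 60 × 1.25². The noncentral t gives 81.1%, 77.9% and 74.7% for equal weights, against 77.5% with one caregiver each.

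**Break-even ρ in other assumed mixes (1/2/3 caregivers).** 95/0/5: 0.37. 90/0/10: 0.40. 90/7/3: 0.46. 80/10/10: 0.49. 90/10/0: 0.55. 70/20/10: 0.56. 80/20/0: 0.60. 70/30/0: 0.65. If multiple caregivers are common it is higher (50/50/0: 0.75), and if all families are equal in size there is no loss at any ρ below 1.

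**Simulation.** Regression with cluster-robust errors in the 80/15/5 mix gave power of 82.9%, 77.8% and 73.8% at ρ = 0.2, 0.5 and 0.8, against about 77.7% with one caregiver each. Type I error at ρ = 0.5 was 5.5% in that mix and 5.2% in a 70/20/10 mix. With an exchangeable correlation estimated from the data and robust errors, type I error stayed near 5%. The gain over equal weighting was about 1 to 2.5 points of power at ρ = 0.3 and 2 to 7 points at ρ = 0.5 to 0.7, with nothing material lost at ρ = 0.1.

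**The case against.** The planned method is standard and valid: robust errors give honest intervals, and simulated type I error is close to nominal. That stands, so this is a matter of efficiency and not of bias or wrong inference.

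Equal weighting is inferred. The approach is to be adapted to caregivers, and an analysis plan that is not shown could add weights or a working correlation. That also stands as a limit. The point does not rest on missing detail, however: the article names a method and states an expectation about power, and on the natural reading the method does not secure the expectation.

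A reader might infer that the article claims extra caregivers can only add power. It does not. The sentence expects a slight gain and says in the same breath that the observations are not independent. A reader might also infer that this trial will lose power. The documents do not support that either, because they give no ICC and no family mix, and below an ICC of about 0.37 the gain was real in every mix tried.

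The assumed mix matters as well. With 80% single-caregiver families and the other 20% all of size three, equal weighting falls to an effective n of 58.8 per arm at ICC 0.5, already below 60. With 80/15/5 or 80/20/0 it is 60.5 or 61.7, still a gain.

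Last, equal weighting estimates the average effect per caregiver, which is a defensible target. Exchangeable weighting gives less weight to each caregiver in a larger family and so shifts the target slightly if the effect depends on family size.

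**Conclusion.** The point holds as a modest loss of efficiency. On the natural reading of {20a}, the caregiver analysis gives up precision whenever family sizes differ and answers within a family are correlated, and the gain expected in {14} is conditional on the ICC. For mixes with 70–95% single-caregiver families the break-even ICC is about 0.37 to 0.65. Above it, losses against one caregiver per family are a few points of power in most mixes (in the 80/15/5 mix at ICC 0.7, 78.2 − 75.5 = 2.7 points). An exchangeable model did not fall below the one-per-family reference in any mix tried. All of this rests on assumed mixes and ICCs and on reading the regression as unweighted.

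**What to change.** For caregiver outcomes, specify a linear model fitted by GEE with exchangeable working correlation within patient, or a random intercept per patient, and keep the robust standard errors. In Sample size {14}, make the statement about slightly greater power conditional on that model, or delete it. The equal-weight regression can stay as a sensitivity analysis, which also covers the average-per-caregiver target.

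The cost is analysis wording only, with no new data. One correlation parameter has to be estimated, and caregivers in larger families are down-weighted. Keeping robust errors protects the interval if the exchangeable form is wrong.

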### Interim analyses {21b}

No interim analyses are planned.

### Methods for additional analyses (e.g. subgroup analyses) {20b}

No subgroup analyses are planned.

We aim to determine whether the PRIME Parkinson intervention is cost-effective. Use of hospital, primary and community care will be ascertained from routine NHS data and participant self-report at follow-up and will be costed using national unit costs, where available. EQ5D-5L responses will be converted into utility scores using value sets recommended at the time of the analysis. Utility scores will be combined with mortality data to estimate quality adjusted life years. In the primary economic analysis, we will estimate the cost-effectiveness of the PRIME Parkinson intervention within the trial follow-up period from the perspective of NHS and social services. Based on national thresholds, we will calculate the net benefit for each patient and use net benefit regression to estimate the incremental net benefit (and 95% confidence intervals) and determine whether the PRIME intervention is cost-effective. In secondary analyses, we will expand the perspective of the analysis to include informal care costs, caregiver quality of life and patient wellbeing measures.

### Methods in analysis to handle protocol non-adherence and any statistical methods to handle missing data {20c}

Missing data will be imputed.

### Plans to give access to the full protocol, participant-level data and statistical code {31c}

Access to the data, and the statistical code used to derive and analyse the primary outcome measure, will be available through application to the Chief Investigator once the primary papers have been submitted. The statistical analyses plan will be made available prior to data analysis through a date stamped website.

## Oversight and monitoring

### Composition of the coordinating centre and trial steering committee {5d}

The Trial Management Group (TMG) meets every 4–6 weeks and is responsible for the day-to-day running of the trial. It is composed of the Chief Investigator and members of the trial team. The trial benefits from methodological input and governance from the Bristol Randomised Trials Collaboration which is a UK Clinical Research Collaboration Registered Clinical Trials Unit.

### Composition of the data monitoring committee, its role and reporting structure {21a}

The TMG reports to a joint Trial Steering Group/Data Management Committee (TSG/DMC) which meets at least annually with a remit to safeguard the interests of the trial participants, investigators and Sponsor, to assess the safety and efficacy of the trial’s interventions and to monitor the trial’s overall conduct. The membership of the TSG/DMC includes statisticians, a member of the Patient and Public Involvement Advisory Group, and an external clinician. In the event of the identification of a significant risk to participant safety, immediate measures would be taken which would include the suspension of recruitment and/or pausing PRIME Parkinson care if advised to do so by the joint TSG /DMC and/or the Sponsor.

### Adverse event reporting and harms {22}

Serious and other adverse events will be reported in accordance with the Good Clinical Practice guidelines and the Sponsor’s Research Related Adverse Event Reporting Policy. Participant safety will be monitored by the TMG, Sponsor and the joint TSG/DMC. The Chief Investigator or delegate will categorise all adverse events according to the accepted definitions of seriousness, expectedness and relatedness. Events expected within this patient population include hospitalisations, prolongation of hospitalisation or death which are probably related to parkinsonism; those related to, or a complication of a pre-existing health condition; hospitalisation for an elective surgical procedure, whether related or unrelated to parkinsonism, and expected side effects of the physical activity intervention including muscular discomfort. The site Principal Investigator is responsible for reporting all adverse events according to the Sponsor guidelines, and will report to the relevant committee as required.

### Frequency and plans for auditing trial conduct {23}

The Sponsor is responsible for monitoring the trial conduct.

### Plans for communicating important protocol amendments to relevant parties (e.g. trial participants, ethical committees) {25}

All protocol amendments will be approved by the Sponsor and the Research Ethics Committee, as relevant. The Chief Investigator or her delegate will highlight and disseminate changes to the trial team.

